| Korean Medicine Hospital |                                                                                                                                                                                                                                                                                                                                                                                                                                                                                                                                                                                                                                                                                                                                                                                                                                                                                                                                                                                                                                                                                                                                                                                                                                                                                                                                                                                                                                                                                                                                                                                                                                                                                                                                                                                                                                                                                                                                                                                                                                                                                                                                                                                                                                                                                                                                                                                                                                                                                                                                                                                                                                                                                                                                                                                                                                                                                                                                                                                                                                                                                                                                                                                                                                                                                                                                                                                                                                                                                                                                                                                                                                                                                                                                                                                                                                                                                                                                                                                                                                                                                                                                                                                                                                                                                                                                                                                                                                                                                                                                                                                                                                                                                                                                                                                                                                                                                                                                                                                                                                                                                                                                                                                                                                                                                                                                                                                                                                                                                                                                                                                                                                                                                                                                                                                                                                                                                                                                                                                                                                                                                                                                                                                                                                                                                                                                                                                                                                                                                                                                                                                                                                                                                                                                                                                                                                                                                                                                                                                                                                                                                                                                                                                                                                                                                                                                                                                                                                                                                                                                                                                                                                                                                                                                                                                                                                                                                                                                                                                                                                                                                                                                                                                                                                                                                                                                                                                                                                                                                                                                                                                                                                                                                                                                                                                                                                                                                                                                                                                                                                                                                                                                                                                                                                                                                                                                                                                                                                                                                                                                                                                                                                                                                                                                                                                                                                                                                                                                                                                                                                                                                                                                                                                                                                                                                                                                                                                                                                                                                                                                                                                                                                                                                                                                                                                                                                                                                                                                                                                                                                                                                                                                                                                                                                                                                                                                                                                                                                                                                                                                                                                                                                                                                                                                                                                                                                                                                                                                                                                                                                                                                                                                                                                                                                                                                                                                                                                                                                                                                                                                                                                                                                                                             |                          |  |  |  |
| Inclusion criteria       | 

</

 |                          |  |  |  |

|                                    |                                                                                                                                                                                                                                                                                                                                                                                                                                                                                                                                                                                                                                                                                                                                                                                                                                                                                                                                      |
|------------------------------------|--------------------------------------------------------------------------------------------------------------------------------------------------------------------------------------------------------------------------------------------------------------------------------------------------------------------------------------------------------------------------------------------------------------------------------------------------------------------------------------------------------------------------------------------------------------------------------------------------------------------------------------------------------------------------------------------------------------------------------------------------------------------------------------------------------------------------------------------------------------------------------------------------------------------------------------|
|                                    | 
 
12. Current smokers or those with history of smoking more than 30 packs/year
 
13. Pregnant or lactating women
 
14. Those who do not use medically acceptable contraception (e.g., intrauterine device with proven pregnancy failure rate in spouse or partner, simultaneous use of barrier method for men or women with spermicide, or surgical procedures, such as vasectomy, tubectomy, tubal ligation, or hysterectomy for oneself or one's partner) during the clinical trial
 
15. Those who participated in other clinical trials within 30 days before participation in this clinical trial
 
16. Those determined by investigators to be ineligible to participate in this trial
 
                                                                                                                                                             |
| Prohibited Concomitant Medications | 
 
1. Antibiotics, antiviral agents, steroids, decongestants, antihistamines, antitussives/expectorants, and other medications expected to relieve nasal congestion
 
2. Medications administered for the same therapeutic purpose as the investigational product or those that may affect the improvement of nasal congestion symptoms.
 
3. Medications containing the same active ingredients (Puerariae Radix, Ephedrae Herba, Zizyphi Fructus, Cinnamomi Ramulus, Paeoniae Radix, Glycyrrhizae Radix et Rhizoma, Zingiberis Rhizoma Crudus, Cnidii Rhizoma, and Magnoliae Flos), even if they are not used for the same therapeutic purpose as the investigational product.
 
                                                                                                                                                                                        |
| Efficacy Outcome Measures          | 
 
• Primary Outcome Measures 
 
1. Change in the WURSS-21-K total score (symptom score + quality of life score) from Baseline to Day 7
 
 
 
• Secondary Outcome Measures 
 
1. Change in the WURSS-21-K total score (symptom score + quality of life score) from Baseline to each time point (excluding Day 7)
 
2. Change in the WURSS-21-K symptom score from Baseline to each time point
 
3. Change in the WURSS-21-K quality of life score from Baseline to each time point
 
4. Change in the Nasal Congestion Severity Score from Baseline to each time point
 
5. Change in the Nasal Symptom Score VAS from Baseline to each time point
 
6. Change in the Systemic Symptom Score VAS from Baseline to each time point
 
 
 
 |

|                         |                                                                                                                                                                                                                                                                                                                                                                                                                                                                                                                                                                                                                                                                                                                                                                                                                                                                                                                                                                                                                                                                                                                                                                                                                                                                                                                                                                                                                                                                                                                                                                                                                                                                                                                                                                                                                                                                                                                                 |
|-------------------------|---------------------------------------------------------------------------------------------------------------------------------------------------------------------------------------------------------------------------------------------------------------------------------------------------------------------------------------------------------------------------------------------------------------------------------------------------------------------------------------------------------------------------------------------------------------------------------------------------------------------------------------------------------------------------------------------------------------------------------------------------------------------------------------------------------------------------------------------------------------------------------------------------------------------------------------------------------------------------------------------------------------------------------------------------------------------------------------------------------------------------------------------------------------------------------------------------------------------------------------------------------------------------------------------------------------------------------------------------------------------------------------------------------------------------------------------------------------------------------------------------------------------------------------------------------------------------------------------------------------------------------------------------------------------------------------------------------------------------------------------------------------------------------------------------------------------------------------------------------------------------------------------------------------------------------|
|                         | 
 
7. Duration of common cold symptoms
 
8. Common cold recovery status on Day 7
 
9. Global Evaluation of Efficacy score on Day 7
 
10. Change in the EQ-5D-5L score from Baseline to Day 7
 
 
• Exploratory Outcome Measures
 
 
1. Change in the WURSS-21-K total score according to the common cold pattern identification (Wind-Cold type, Wind-Heat type, or Other types).
 
                                                                                                                                                                                                                                                                                                                                                                                                                                                                                                                                                                                                                                                                                                                                                                                                                                                                                                                                                                                                                                                                                                                                                                                                                                                                                                                                                                                                                   |
| Safety Outcome Measures | 
 
1. Adverse events
 
2. Vital signs
 
3. Laboratory tests
 
                                                                                                                                                                                                                                                                                                                                                                                                                                                                                                                                                                                                                                                                                                                                                                                                                                                                                                                                                                                                                                                                                                                                                                                                                                                                                                                                                                                                                                                                                                                                                                                                                                                                                                                                                                                                        |
| Statistical Analysis    | 
• General Principles of Statistical Analysis
 
 
1. Definition of Analysis Sets 
For the analysis of data from this clinical trial, efficacy analysis will primarily use the Full Analysis Set (FAS) as the main method, and the Per Protocol Set (PPS) analysis will be used as a supplementary confirmation when necessary.
 
 
1) The FAS is defined according to ITT principle, which includes all randomized subjects who received at least one dose of the investigational product and have at least one post-baseline efficacy measurement. All data obtained from these subjects will be included in the analysis. However, subjects who do not meet a pre-established criteria will be excluded. The exclusion criteria for the FAS are as follows: 
 
i. Subjects who violate the inclusion or exclusion criteria
 
ii. Subjects who did not take the investigational product even once
 
iii. Subjects who did not provide any data after screening
 
 
 
2) The PPS analysis set consists of a subset of subjects from the FAS who have a drug compliance rate of at least 70% of the total investigational product dose, completed the entire trial process as specified in the protocol, and have no major protocol violations that could affect the results. The definition of major violations is based on the content described in section 7.1 of this protocol.
 
 
For the safety analysis of the data obtained from this clinical trial, all data from subjects who received at least one dose of the investigational product after randomization and underwent a safety evaluation will be included in the analysis. For safety analysis, subjects will be analyzed in the group they actually received treatment in.
 
 
 |

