#### 2) Rationale

This clinical trial is designed to evaluate the efficacy and safety of GGTCS for patients with nasal congestion due to the common cold. The primary outcome measure is the WRUSS-21-K. The change in the WRUSS-21-K from baseline to Day 7 (after a total of 21 doses, 3 times a day for 7 days) will be compared between the test group (GGTCS) and the control group (placebo).

The hypothesis for this clinical trial is as follows:

[Hypothesis]  $H_0$ (Null Hypothesis):  $\mu_t = \mu_c$  vs.  $H_1$ (Alternative Hypothesis):  $\mu_t \neq \mu_c$

$\mu_t$  : The mean change in the WRUSS-21-K score from baseline to Day 7 in the test group.

$\mu_c$  : The mean change in the WRUSS-21-K score from baseline to Day 7 in the control group.

Table 1. Change in WRUSS-21-K of Eungyo-san, Sams0-eum, placebo between pre- and post-treatment.

|                   | Pre-Treatment | Post-Treatment | Change (Before-After)* |
|-------------------|---------------|----------------|------------------------|
| Eungyo-san (n=44) | 56.28(30.47)  | 13.86(22.43)   | 44.00(22.27)           |
| Sams0-eum (n=42)  | 54.74(30.98)  | 17.05(24.29)   | 40.12(18.78)           |
| Placebo (n=42)    | 66.48(31.64)  | 33.33(30.02)   | 29.09(21.89)           |

\*: Change adjusting WRUSS-21-K score of baseline.

Previous studies (K.-I. Kim, M. Hong) showed that the mean (standard deviation) change in the WRUSS-21-K score from pre- to post-treatment was 29.09 (21.89) for the placebo group, 44.00 (22.27) for the Eungyo-san treatment group, and 40.12 (18.78) for the Samso-eum treatment group. The mean difference in effect was 14.91 for the Eungyo-san treatment group compared with the placebo group, with a pooled standard deviation of 22.09. The mean difference in effect for Samso-eum compared with the placebo group was 11.03, with a pooled standard deviation of 20.39. In this clinical trial, the significance level ( $\alpha$ ) was set at a two-sided 5%, and the power ( $1-\beta$ ) is 80%. Based on the results of the previous studies, the effect difference is set at 10 and the standard deviation at 21. The calculated number of subjects required to confirm the effect of the GGTCS group compared with the placebo group is as follows.

$$\left\{ \frac{2 \left( z_{1-\frac{\alpha}{2}} + z_{\beta} \right)^2 * \sigma^2}{|\mu_T - \mu_c|} \right\} = \left\{ \frac{2(1.96 + 0.84)^2 * 21^2}{10^2} \right\} = 69.227 \approx 70$$

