## 9. Methods and Administration

### 9.1. Investigational Product Administration

The investigational product will be administered once per packet (1 pack) three times a day, before or between meals. The total administration period is a maximum of 7 days (21 packets). The daily dose for each group is as follows. If the cold symptoms disappear before the maximum 7-day administration period, subjects will stop taking the medication and return the remaining investigational products.

- ✓ Test Group (GGTCS): 1 packet (3g) per dose, 3 times/day, for a maximum of 7 days.
- ✓ Control Group (Placebo): 1 packet (3g) per dose, 3 times/day, for a maximum of 7 days.

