#### 9.4. Compliance Assessment

To assess medication compliance with the investigational product, the number of doses taken and returned will be checked. Subjects should bring the empty packets and any unconsumed medication from the previous visit, along with their completed cold diary. The investigator will confirm whether the subject took the provided medication and will instruct them to return any remaining medication at the visit, and to avoid overdosing or losing the product. Medication compliance (%) will be calculated as shown below, recorded in the CRF to one decimal place. Compliance of 70% or more is considered "acceptable".

$$\text{Compliance (\%)} = \frac{\text{Number of investigational products actually taken}}{\text{Number of investigational products that should have been taken}} \times 100$$

When calculating the number of investigational products that should have been taken, the rule is to start taking the medication on the evening of the prescription date and to continue taking it until the evening before the next visit. The compliance will be calculated based on the amount that should have been taken and the amount actually taken from the evening of the prescription date until the evening before the next visit. If the subject stops taking the medication due to symptom resolution, compliance will be calculated based on the amount taken from the evening of the prescription date until the evening of the day before the symptoms resolved.

Subjects with a final medication compliance of less than 70% will be excluded from the PP analysis.

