## **11. Data Analysis and Statistical Analysis**

### **11.1. General Principles of Statistical Analysis**

#### **11.1.1. Definition of Analysis Sets**

The efficacy analysis of this clinical trial will primarily use the Full Analysis Set (FAS), with the Per-Protocol Set (PPS) used for supplementary verification as needed.

- 1) FAS: Adhering to the Intention-To-Treat (ITT) principle, the FAS includes all randomized subjects who have taken the investigational product at least once and for whom efficacy data have been collected at least once. Data from subjects not meeting pre-established criteria will be excluded. The exclusion criteria for the FAS analysis are as follows:
  - Violation of inclusion or exclusion criteria
  - Subjects who did not take the investigational product even once
  - Subjects who did not provide any data after screening
- 2) PPS: The PPS consists of subjects from the FAS who have a medication compliance of 70% or more, have completed all procedures as specified in the protocol, and have no major protocol violations that could affect the results. The definition of major violations follows the details in Section 7.1 of this protocol.

The safety analysis will include data from all subjects who have taken the investigational product at least once after randomization and for whom a safety assessment was performed. The analysis will be conducted based on the group to which subjects were actually assigned.

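### The synopsis defines per-protocol compliance against the total dose, which contradicts sections 9.4 and 11.1.1 and, read literally, drops fully adherent subjects who recover by about Day 5

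*Protocol*

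**What the plan says.** Four places in the protocol bear on who enters the PPS on compliance grounds.

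- **Synopsis, Statistical Analysis, Definition of Analysis Sets.** The PPS is made up of FAS subjects "who have a drug compliance rate of at least 70% of the total investigational product dose", who also completed the trial and had no major violation.
- **Section 11.1.1.** "The PPS consists of subjects from the FAS who have a medication compliance of 70% or more". The other conditions are the same, but no total dose is mentioned.
- **Section 9.1.** The course is at most 7 days, or 21 packets. "If the cold symptoms disappear before the maximum 7-day administration period, subjects will stop taking the medication and return the remaining investigational products".
- **Section 9.4.** Compliance is packets taken divided by packets that should have been taken, counted from the evening of the prescription date. "If the subject stops taking the medication due to symptom resolution, compliance will be calculated based on the amount taken" up to the evening before the day of resolution. Subjects below 70% are then left out of the PP analysis.

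Section 5.3 describes the Day 7 comparison as made "after a total of 21 doses, 3 times a day for 7 days". The sample-size table there labels its 70 per group as the PP population. The synopsis and section 11.1.1 both make the FAS the main efficacy set and give the PPS a supporting role, to be used when needed.

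**The concern.** The synopsis and section 9.4 use the same 70% threshold with different denominators. For a subject who completes the full course the difference hardly matters. For a subject who stops because the cold has gone, as section 9.1 directs, it decides membership of the PPS: the fixed denominator counts the untaken packets as non-compliance, and the shortened one does not.

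The subjects affected are not a random subset. They are the fastest recoverers, and both duration of symptoms and recovery status on Day 7 are secondary outcomes. A set defined by the literal synopsis text would be selected on a post-randomisation event that the treatment is meant to influence, and the comparison within it would no longer be protected by randomisation. There is also a practical problem: two analysts could build different per-protocol sets from the same data, each citing the protocol.

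**Working it through.** **The plan's own figure.** Section 5.3 uses a difference of 10, an SD of 21, two-sided 5% and 80% power. n = 2(z₀.₉₇₅ + z₀.₈₀)² × 21² / 10² = 69.227, rounded up to 70 per group. Allowing for 20% dropout, 70 / 0.80 = 87.5, rounded up to 88. Both figures reproduce.

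**Threshold under the literal synopsis.** The synopsis gives no packet number; the maximum of 21 comes from section 9.1. 0.70 × 21 = 14.7, so at least 15 packets.

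**Packets taken by a fully adherent early resolver.** Section 9.4 starts the count on the evening of Day 0 and, for resolution on Day r, ends it on the evening of Day r − 1. That is one packet on Day 0 and three on each later day: packets = 1 + 3(r − 1).

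| Resolution day | Packets | % of 21 (literal synopsis) | In PPS by synopsis | Compliance by 9.4 |
|---|---|---|---|---|
| 1 | 1 | 4.8 | no | 100% |
| 2 | 4 | 19.0 | no | 100% |
| 3 | 7 | 33.3 | no | 100% |
| 4 | 10 | 47.6 | no | 100% |
| 5 | 13 | 61.9 | no | 100% |
| 6 | 16 | 76.2 | yes | 100% |
| 7 | 19 | 90.5 | yes | 100% |

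The 9.4 column takes both parts of the fraction to stop at the same evening. The sentence on early stopping names only the amount taken, but the denominator is what should have been taken, and section 9.1 prescribes nothing after resolution.

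**Sensitivity to the day count.** If dosing is counted in full days of three packets, four days give 12 (57.1%, dropped) and five days give 15 (71.4%, kept). The boundary moves by about a day, so it is fairly put as about Day 5.

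**Possible loss of precision (assumed shares).** The protocol gives no rate of early resolution. If 10%, 20% or 30% of the 70 per group were dropped, 63, 56 or 49 would remain. Power = Φ(10 / (21√(2/n)) − 1.96) is then about 76%, 71% or 65%, against 80% with 70.

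**Direction of bias (assumed inputs).** Take the section 5.3 placebo change of 29.09 and add the planned 10, giving 39.09 for GGTCS. Assume early resolvers improve by 55 points on average. After removing a share r, the remaining mean is (m − 55r) / (1 − r).

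- Removing 30% from GGTCS and 15% from placebo: (39.09 − 16.50) / 0.70 = 32.27 and (29.09 − 8.25) / 0.85 = 24.52, a difference of about 7.8.
- Removing 25% from each: 10 / 0.75 = 13.3.

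The PPS difference can therefore fall below or rise above 10, depending on shares that the protocol does not supply.

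**The case against.** The strongest reply is that the body already gives a workable rule. Section 9.4 defines compliance, deals with stopping for resolution and states the PP exclusion, and section 11.1.1 repeats the 70% threshold without a total dose. The synopsis borrows a term that only section 9.4 defines, so its reference to the total dose may be no more than a loose summary. On that reading no adherent early resolver is lost. Moreover, the PPS only supports an FAS analysis that neither compliance rule affects.

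Much of this stands. The documents show a contradiction, not a settled rule that removes these subjects. It does not dispose of the point, because the synopsis is part of the same protocol, gives a different denominator in plain words, and nothing says which text prevails.

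A reader might also infer three stronger things that the documents do not support:

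- **That everyone who recovers early is removed.** Adherent subjects resolving on Day 6 or 7 clear 15 packets even under the literal synopsis.
- **That the PPS would be biased in a known direction.** The calculation above goes either way on assumed inputs.
- **That the 70 per group could not be reached.** This needs an unstated early-resolution rate, and it needs the whole 20% allowance to be used up by other losses. Section 7.1 already lists compliance under 70% as a ground for dropout, so part of any such loss may lie inside the step from 88 to 70.

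**Conclusion.** The contradiction is real and the synopsis text is wrong as it stands. Read against the 21-packet maximum, it would exclude fully adherent subjects whose cold resolves on Days 1 to 5, with at most 13 packets (61.9%). Sections 9.4 and 11.1.1 keep all of them. Exclusion under the synopsis would depend on how quickly a subject recovers, which the trial also analyses as an outcome.

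The consequences are bounded. The primary analysis on the FAS does not change. The effect on the PPS cannot be sized from the documents. The power figures of 76% to 65% rest on assumed removals of 10% to 30% taken from the planned 70 per group, and they illustrate the range without predicting a result. The Day 5 boundary rests on the evening start and cut-off in section 9.4.

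**What to change.** In the synopsis definition of the PPS, replace the reference to the total dose with compliance of at least 70% as calculated in section 9.4. This brings the synopsis into line with section 11.1.1 and leaves one denominator for the whole document.

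Separately, reconcile the statement in section 5.3 that the Day 7 comparison follows 21 doses with section 9.1, under which some subjects stop sooner. Which text should change there is for the investigators to decide.

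The cost is a wording amendment. Packet counts and the date of resolution are already collected, so no new data are needed and the sample size does not change. It should be made before unblinding, so that the choice of denominator cannot be influenced by the results.
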